### Randomization and allocation concealment

One hundred twenty subjects will be randomly assigned to four groups. The random numbers are generated by the computer and sealed in opaque, airtight envelopes to form a completely random distribution scheme. According to registration order, the subject management center will open the corresponding serial number envelope in sequence and assign the patients to the corresponding experimental group. The acupuncture operators will treat the patients according to the corresponding treatment plan.

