## Methods/design

### Study design

This will be a parallel group randomized controlled trial. The study will recruit 120 patients with insomnia from the Affiliated Hospital of Chengdu University of TCM and the Third Affiliated Hospital of Chengdu University of TCM. Meanwhile, ten healthy subjects who meet the study criteria will be recruited as the healthy control group. The patients enrolled will be randomly assigned to a control group, an electroacupuncture on HT 7 group (EA-SM group), an electroacupuncture on SP 6 group (EA-SY group), and an electroacupuncture on HT 7 and SP 6 group (EA-SS group). The allocation ratio is 1:1:1:1, with 30 subjects in each group. All patients will be asked to sign the consent form before the trial. Patients in the intervention groups will be given ten rounds of electroacupuncture stimulation on corresponding acupoints for 2 weeks, five times per week, with 2 days of rest between the two treatment courses. Patients in the control group will also receive the same two courses, ten rounds of compensatory acupuncture therapy after the 2-week waiting period for treatment. The healthy control group will not be given any intervention. The overall schematic and study design are presented in Fig. 1, and the schedule of enrollment, intervention, and assessments is shown in Fig. 2, according to the Standard Protocol Items: Recommendations for Interventional Trials (SPIRIT) 2013 statement [18].

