### Sample size

This study sample size is calculated on the basis of a ratio of 1:1:1:1 between the intervention groups and the control group. Though there are four study groups, the study can be regarded as a comparison between each intervention group and the control group. This study refers to the method of sample size estimation in this paper [20]. In those studies, the sample sizes are based on studies that investigated the effect of acupuncture-related treatment on insomnia using the Sleep Dysfunction Rating Scale (SDRS) as a major outcome [21, 22], and the number of participants required for each group is 30 or 31. In addition, in the study [21], the mean change in SDRS between the intervention and control groups was 2.69, and the standard deviation was estimated from the means and the standard deviations of intervention (− 14.80 ± 3.52) and control groups (− 12.11 ± 2.38). On the basis of a two-tailed alpha error of 5% and with a statistical power of 90%, the calculated sample size is based on the equation:
$$ N=\frac{2\times {\left(\frac{Z\alpha}{2}+ Z\beta \right)}^2\times {\sigma}^2}{\delta^2} $$$$ N=\frac{2\times {\left(1.96+1.28\right)}^2\times {3.00}^2}{2.69^2}=26.11 $$

Therefore, this study’s sample size is 120, assuming a 15% dropout rate, and all 120 participants will be randomly assigned, with 30 subjects in each group.

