## Data analysis

Statistical analysis includes the actual number of subjects, cases of shedding and exclusion, demographic and other baseline characteristics, compliance analysis, safety assessment, insomnia and emotional state scores, SL, TST, and quantity analysis of serum neurotransmitters and hormones. IBM SPSS Statistics for Windows version 19.0 software (IBM Corp., Armonk, NY, USA) will be used for statistical analysis. We will adopt univariate analysis of variance to analyze the age, height, weight, scale score, SL, TST, neurotransmitter and hormone content, and so forth, and we will use the chi-square test to analyze gender comparison and the rank-sum test to analyze the course of disease. *P* < 0.05 will be considered as the standard of statistical significance. Serum will be analyzed by liquid chromatography–mass spectrometry, and the serum metabolic biomarkers of insomnia will be screened using MetaX metabolomic data analysis software (BGI Genomics Co. Ltd., Shenzhen, China).

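### Patients come from two hospitals, but the allocation names no stratification and the stated ANOVA no hospital factor; adding hospital to the model is a modest, nearly free gain in precision

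*Protocol article*

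**What the plan says.** Three sections of the protocol article bear on this.

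- **Study design.** Patients are recruited "from the Affiliated Hospital of Chengdu University of TCM and the Third Affiliated Hospital of Chengdu University of TCM". The section adds: "The allocation ratio is 1:1:1:1, with 30 subjects in each group". The split of patients between the hospitals is not given.
- **Randomization and allocation concealment.** "The random numbers are generated by the computer and sealed in opaque, airtight envelopes to form a completely random distribution scheme". Following the order of registration, "the subject management center will open the corresponding serial number envelope in sequence". This is one central sequence. No stratum, block or hospital-specific list is named.
- **Data analysis.** "We will adopt univariate analysis of variance to analyze the age, height, weight, scale score", followed by sleep latency, total sleep time and the serum measures. Hospital is not named as a factor or covariate.

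The Trial status section reports 115 participants recruited, with recruitment still open. It does not say whether that count includes the ten healthy controls.

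**The concern.** If SDRS differs on average between patients of the two hospitals, for whatever reason, an unstratified list leaves the hospital mix of each arm to chance. A model without hospital then does two things. It keeps the between-hospital variation in the residual, which widens every arm comparison. It also leaves a chance difference in hospital mix inside the one realised contrast that the trial will report.

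The trial asks more than whether each active arm beats the waiting control. The Background asks whether the two points together differ from either alone, and how the points compare with each other. Lost precision matters most where the differences sought may be small.

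**Working it through.** **1. The plan's own figure.** The Sample size section gives a difference of 2.69, an SD of 3.00, two-sided alpha of 5% and 90% power:

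n = 2 × (1.96 + 1.28)² × 3.00² / 2.69² = 26.11 per group.

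This reproduces. At 30 per arm the standard error of a pairwise difference is 3.00 × √(2/30) = 0.775, and power is 0.935 by the normal approximation.

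**2. Assumptions, because the article is silent.** The hospital split is taken as 50:50, with 70:30 and 85:15 as alternatives. The difference between hospitals in mean SDRS, D, is taken as 0, 1.5 or 3.0 points (up to one planning SD). The SD of 3.00 is treated as the SD within hospital. The list is taken as a random order with 30 per arm.

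**3. Chance imbalance between two given arms.**

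| Hospital split | SD of the difference in hospital share | Probability that the difference is 20 points or more |
|---|---|---|
| 50:50 | 13 points | 0.16 |
| 70:30 | 12 points | 0.12 |
| 85:15 | 9 points | 0.05 |

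At 50:50 the realised contrast is shifted with SD 0.130 × D. That is 0.19 point at D = 1.5 and 0.39 point at D = 3.0, against the standard error of 0.775 and the target of 2.69.

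**4. Loss of precision without the hospital term, 50:50 split.** The between-hospital variance is D² × 0.5 × 0.5 = D²/4. The variance ratio is R = (9 + D²/4)/9, the standard error rises by the factor √R, and the loss of effective sample size is 1 − 1/R.

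| D (points) | R | Rise in SE | Loss of effective sample size |
|---|---|---|---|
| 0 | 1 | 0% | 0% |
| 1.5 | 9.5625/9 = 1.0625 | 3% | 6% |
| 3.0 | 11.25/9 = 1.25 | 12% | 20% |

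Steps 3 and 4 show the same quantity in two ways and must not be added. At D = 3.0, √(0.775² + 0.39²) = 0.87, which is 1.12 × 0.775.

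**5. Power and type I error.** Simulation of a two-arm comparison: 30 per arm, 50:50 split, true difference 2.69 for power, 4,000 runs per cell.

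| D (points) | Power, no hospital term | Power, hospital in the model | Type I error, no hospital term |
|---|---|---|---|
| 0 | 0.926 | 0.919 | 0.050 |
| 1.5 | 0.908 | 0.924 | 0.059 |
| 3.0 | 0.856 | 0.919 | 0.050 |

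The Monte Carlo standard error of the type I figures is about 0.0034. The 0.059 is somewhat high, but there is no trend: at D = 3.0, where a real effect would be larger, the figure is 0.050. Power with the term stays at about 0.92 whatever D is. The small deficit at D = 0 is of the order of the simulation error.

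**The case against.** The strongest reply is that the Data analysis section is a condensed paragraph and that site terms are ordinary content of an analysis plan, which is not shown. That stands as a limit: if the full plan already includes hospital, the point is closed. What remains is that the article names its allocation scheme and its model for the scale scores, and hospital appears in neither.

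It can also be said that unstratified central allocation is legitimate with two sites and 30 per arm, and that a 3.0-point hospital difference is large, since it exceeds the target effect of 2.69. Both are fair. At 1.5 points the loss is only 3% in standard error, and unadjusted power stays above 90%. In addition, if the planning SD of 3.00 is already a total SD, power does not fall below plan, and the hospital term is a gain above it.

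A reader might infer more than the article supports:

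- **That the list cannot give 30 per group.** The Sample size section says "all 120 participants will be randomly assigned, with 30 subjects in each group". Under simple randomisation, exactly 30 in all four arms would have probability 0.00076. But completely random can also describe 120 envelopes with fixed totals of 30 in random order, which gives 30 per arm with certainty. No contradiction is shown.
- **That operators or raters differ by hospital.** The article says where patients are recruited, not that treatment or rating is split by hospital. The Quality control section describes common training and designated raters.
- **That the comparisons are biased or the test invalid.** Chance imbalance does neither; the ordinary standard error already covers it.
- **That a quarter of the sample is lost at 3.0 points.** The variance rises by 25%, which is a 20% loss of effective sample size.

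**Conclusion.** The point holds as a modest improvement to the stated analysis, not as a flaw in validity. With two recruiting hospitals, no stratification named and no hospital factor in the ANOVA, any hospital difference in SDRS goes into the error term. With an even split and 30 per arm, the cost runs from nothing (no hospital difference) through 3% in standard error (1.5 points) to 12% (3.0 points). In the same order, pairwise power is about 0.93, 0.91 and 0.86, against about 0.92 with the term. A more uneven split makes the cost smaller. The hospital differences and the split are assumptions; the article supports no particular value.

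**What to change.** Add hospital as a fixed factor to the SDRS model and to the models for the other continuous outcomes, and report the number of patients by arm and hospital. Fix this before the outcome data are examined by arm.

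The cost is one degree of freedom per model and a variable that the trial should already hold for every patient. If the hospitals do not differ, practically nothing is lost.

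Changing the allocation list is no longer worthwhile. Even if the 115 recruited include all ten healthy controls, at least 105 of the 120 patients are already allocated. Nor would stratification replace the model term: with a stratified list and no hospital term, the simulated type I error at a 3.0-point difference was 0.027, so the test would be conservative.

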### Blinding

The participants will be blinded in this trial by being treated in an isolated room. The acupuncture operators, outcome assessors, and statisticians who perform the statistical analyses will be blinded to group assignment.

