**Fig. 2 Fig2:**
[figure not shown]
Study schedule of enrollment, interventions, and assessments. The template is derived from the Standard Protocol Items: Recommendations for Interventional Trials (SPIRIT) 2013 statement. The patients in the control group will finish the assessments and then receive compensatory acupuncture therapy at week 3 after the 2-week waiting period (week 1, week 2). *EA-SM Group* electroacupuncture on Shenmen (HT 7), *EA-SY Group* electroacupuncture on Sanyinjiao (SP 6), *EA-SS Group* electroacupuncture on Shenmen (HT 7) and Sanyinjiao (SP 6), *SDRS* Sleep Dysfunction Rating Scale, *ISI* Insomnia Severity Index, *ESS* Epworth Sleepiness Scale, *SAS* Zung Self-Rating Anxiety Scale, *SDS* Zung Self-Rating Depression Scale, *PSG* polysomnography

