### Interventions

Patients in the three intervention groups will be given ten rounds of electroacupuncture stimulation on corresponding acupoints for 2 weeks, five times per week, with 2 days of rest between the two treatment courses. Patients in the insomnia control group will also receive the same two courses comprising ten rounds of compensatory acupuncture therapy after the 2-week waiting period for treatment. The healthy control group will not be given any intervention.

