#### Selection of the acupoints

EA-SM group: HT 7, auxiliary acupuncture point 1EA-SY group: SP 6, auxiliary acupuncture point 2EA-SS group: HT 7, SP 6, auxiliary acupuncture point 1, auxiliary acupuncture point 2

All the acupoints above are selected symmetrically on the left and right sides of the limbs.

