#### Therapeutic procedures

Electroacupuncture will be performed by trained acupuncture operators. A sterile acupuncture needle will be inserted into HT 7 at a depth of 0.3 to 0.5 *cun* (length 25 mm, diameter 0.25 mm; Huatuo, Suzhou Medical Supply Factory Co. Ltd., Suzhou, China), into SP 6 at a depth of 0.5 to 1 *cun* (length 40 mm, diameter 0.25 mm; Huatuo, Suzhou Medical Supply Factory Co. Ltd., Suzhou, China) with the de qi sensation (a compositional sensation including soreness, numbness, distention, and heaviness), and into the auxiliary points to a depth of 0.2 *cun* (length 13 mm, diameter 0.18 mm; Huatuo, Suzhou Medical Supply Factory Co. Ltd., Suzhou, China) without the de qi sensation. Then the operators will apply electroacupuncture stimulation (SDZ-II electroacupuncture therapy apparatus; Huatuo, Suzhou Medical Supply Factory Co. Ltd., Suzhou, China) by connecting HT 7 and the auxiliary point 1 as one pair of electrodes and connecting SP 6 and the auxiliary point 2 as another, using density-wave electrical stimulation with a frequency of 5 Hz to 25 Hz and current intensity between 1.0 mA and 1.5 mA. The output strength of electroacupuncture will be set according to the maximum tolerated intensity and the comfort feeling of each subject. The treatments will last 30 min. They will be given ten times for 2 weeks, five times per week, with 2 days of rest between the two treatment courses.

The subjects in the three intervention groups will be prohibited from receiving any other relevant treatment during the trial period. In our study, no drug combination that can improve sleep is permissible. All relevant treatments and medication compliance will be recorded in the case report form.

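### The protocol says participants and acupuncture operators are blinded, but an untreated waiting-list control and arm-specific needling sites rule out both

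*Protocol article*

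**What the plan says.** The Blinding section of the Protocol article has two sentences, both without qualification. On patients: "The participants will be blinded in this trial by being treated in an isolated room". On everyone else: "The acupuncture operators, outcome assessors, and statisticians who perform the statistical analyses will be blinded to group assignment".

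Other sections describe what each party does.

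- **Control arm.** Interventions gives the insomnia control group "ten rounds of compensatory acupuncture therapy after the 2-week waiting period for treatment". The Fig. 2 legend fixes the order: "The patients in the control group will finish the assessments and then receive compensatory acupuncture therapy at week 3 after the 2-week waiting period". No sham procedure is described in the article.
- **Operators.** Randomization and allocation concealment says: "The acupuncture operators will treat the patients according to the corresponding treatment plan". Selection of the acupoints defines the arms by site: "EA-SM group: HT 7, auxiliary acupuncture point 1EA-SY group: SP 6, auxiliary acupuncture point 2EA-SS group: HT 7, SP 6", with both auxiliary points added in the combined arm. Under Therapeutic procedures the operators insert the needles and then apply the current "by connecting HT 7 and the auxiliary point 1 as one pair of electrodes and connecting SP 6 and the auxiliary point 2 as another".

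The Sample size section treats the trial as a set of comparisons of each EA arm with the control group. The limitations paragraph at the end of the Discussion deals only with untargeted metabolomics and does not mention blinding.

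**The concern.** The article claims a protection against bias that its own design cannot provide, and claims it for the comparison on which the trial is sized. Patients who know they are being treated may report improvement because they expect it. Patients who know they are waiting may report less. A reader who trusts the Blinding section could take an EA-minus-control difference as the effect of stimulating particular acupoints. Without blinding, that difference is a total effect: whatever the points do, plus expectation, attention and the experience of being treated.

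**Working it through.** The core of the check is a comparison of sections, role by role.

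1. **Participants, EA versus control.** The stated means of blinding is the room in which treatment takes place. A control patient receives no treatment in weeks 1 and 2 and is assessed before the first needle (Interventions; Fig. 2 legend). An EA patient has ten 30-minute sessions of needling and current (Therapeutic procedures). A room cannot hide from either patient which of these is happening.

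2. **Participants, between EA arms.** HT 7 is at the wrist and SP 6 on the lower leg (Location of the acupoints), so patients can feel where they are needled. They might be kept unaware of what the other arms receive, but the article does not say so.

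3. **Operators.** The EA arms are defined by site: wrist, lower leg or both. The person who inserts the needles and connects the matching electrode pairs knows the arm from the task itself.

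4. **Outcome assessors and statisticians.** Blinding them is feasible, and nothing in the article contradicts it.

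5. **Exposure of the outcomes.** The article does not say plainly whether the SDRS is rated by the patient or by an assessor. Quality control and guarantee says designated people complete the scales. The SDRS covers sleep quality and insomnia-related discomfort (Major outcome measures), so even a blinded rater works from what an unblinded patient reports. The Zung anxiety and depression scales are self-rated, and the Measure Your Medical Outcome Profile is self-reported (Secondary outcome measures). Polysomnography and serum measures are less exposed.

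6. **Sample size.** The plan's figure reproduces: 2 × (1.96 + 1.28)² × 3.00² / 2.69² = 188.96 / 7.236 = 26.11 per group, and 26.11 × 1.15 = 30.03, in line with 30 per group. Blinding does not enter this formula, so the sample size does not change.

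7. **Sensitivity, for illustration only.** The article gives no expectation effect, so *b* is assumed. Take a true EA effect of zero, SD 3.00 and 30 per group. Then SE = 3.00 × √(2/30) = 0.775, and the chance of two-sided p < 0.05 in one EA-versus-control comparison is 1 − Φ(1.96 − b/SE) + Φ(−1.96 − b/SE).

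| Assumed *b* (SDRS points) | Chance of p < 0.05 |
|---|---|
| 0 | 5% |
| 0.5 | 9.9% |
| 1.0 | 25% |
| 1.5 | 49% |
| 2.0 | 73% |

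This shows how sensitive the comparison is to such a bias. It does not estimate the bias.

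8. **Needle counts.** All points are used on both sides. A single-point arm has 2 points × 2 sides = 4 needles. The combined arm has 4 points × 2 sides = 8, twice as many.

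9. **Synergy contrast.** On an additive scale, synergy or antagonism is EA-SS − EA-SM − EA-SY + control, which needs the control arm. If an expectation gain *e* were equal in the three EA arms and absent in controls, it would add e − e − e + 0 = −e to this contrast on the improvement scale. The limitation therefore applies here too.

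**The case against.** Several points can be made in the plan's defence.

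- An isolated room may stop EA patients from comparing treatments, and envelopes are opened by a subject management center rather than by the operators. Both are useful. Neither hides EA from waiting, and neither hides the arm from the person needling it. The Blinding section does not limit its claim to these narrower purposes.
- A blinded assessor protects against rater bias, and some secondary outcomes are objective. This stands, and it narrows the concern to outcomes that depend on patient report. It does not remove it for the SDRS.
- The correction changes no sample size, endpoint or test. This also stands. The waiting-list design itself is not challenged, only its description and what can be concluded from it.

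A reader might infer more than the article supports.

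- **That the trial will be reported as double-blind.** The term does not appear. The article calls the trial a parallel group randomised controlled trial, and how results will be presented is not known.
- **That the sizing study shows how large the non-specific response is.** Its control arm changed by 12.11 points against 14.80 in the intervention arm, a ratio of 12.11/14.80 = 82%. The article does not say what that control received, so the ratio cannot be read as a non-specific share.
- **That comparisons between EA arms are free of the problem and should alone support acupoint conclusions.** The arms differ in site and number of needles, and dropping the control arm would leave the stated synergy question unanswerable.

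**Conclusion.** The point holds. The Blinding section is wrong as written for participants (EA versus waiting) and for operators, and the article's own description of the design shows it. Blinding of outcome assessors and statisticians is not disputed. The consequence is a limit on interpretation: EA-versus-control differences on the SDRS and the self-report scales cannot, by themselves, be read as acupoint-specific effects. No size can be attached, because the article gives nothing from which an expectation effect could be derived, and the sensitivity figures rest entirely on assumed values. The conclusion relies on two readings of the text: that no sham is given to controls during the wait, and that SDRS content depends on patient report whoever completes the form.

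**What to change.** 1. Rewrite the Blinding section to say that participants are not blinded to EA versus waiting and that operators are not blinded. Limit the blinding claim to outcome assessors and statisticians. Add that assessors were separate from operators only if that was so in conduct, because the article does not say it. If EA patients were kept unaware of anything, such as what the other arms received, state what.
2. Add to the limitations paragraph of the Discussion that EA-versus-control differences are total effects including expectation, and are not by themselves evidence of an acupoint-specific effect. Note that polysomnography and serum outcomes are less exposed.
3. Keep the control arm for the synergy or antagonism question, with the same caution.
4. Note that comparisons between EA arms, although every patient is needled, also differ in site and number of needles (8 in the combined arm against 4 in each single-point arm).

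The cost is a few sentences and a narrower conclusion. Trial status reports that 115 participants have already completed the intervention, and nothing here changes conduct, sample size or analysis. The text should be corrected before results are reported.
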